## Abstract

**Background:**

Transgender women face significant health inequities. Facial feminization surgery is an intervention that aligns craniofacial structures with female anatomical norms and gender identity. Although international studies suggest that facial feminization surgery improves psychosocial outcomes, most studies have focused on aesthetic results or relied on generic quality-of-life instruments that have not been validated for this population. In Chile, no study has evaluated the multidimensional impact of facial feminization surgery using patient-centered measures combined with objective cephalometric and photometric analyses. Moreover, no validated Spanish-language quality-of-life instrument exists for transgender women undergoing this surgery.

**Objective:**

This study aims to (1) develop and validate a culturally appropriate quality-of-life questionnaire for transgender women undergoing facial feminization surgery in Chile, and (2) evaluate postoperative changes in quality of life, perception of facial femininity, and cephalometric and photometric parameters.

**Methods:**

The study will include 2 methodological phases: a cross-sectional validation study and a longitudinal cohort study. Phase 1 involves questionnaire development and validation, following the COSMIN (Consensus-Based Standards for the Selection of Health Measurement Instruments) guidelines, with a systematic literature review conducted according to the PRISMA (Preferred Reporting Items for Systematic Reviews and Meta-Analyses) guidelines, expert panel content validation, pilot testing, and psychometric evaluation in a cohort of ≥200 transgender women. Phase 2 is a longitudinal cohort study conducted at San Juan de Dios Hospital in Santiago, Chile, following the STROBE (Strengthening the Reporting of Observational Studies in Epidemiology) guidelines. Thirty transgender women scheduled for facial feminization surgery will be assessed at baseline and 12 months postoperatively. Outcomes include quality of life, self-perceived and third-party–rated femininity, and cephalometric and photometric changes (using cone beam computed tomography). Data analyses include exploratory and confirmatory factor analyses, Cronbach α, paired 1-tailed *t* tests or Wilcoxon signed-rank tests, chi-square or Fisher tests, and linear regression models.

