The surgery involves modifications to both hard and soft tissues, which can be assessed using cone beam computed tomography (CBCT) and standardized clinical photography. The international literature identifies the frontal-naso-orbital complex (including the forehead, supraorbital crest, frontomalar prominence, temporal ridges, and frontonasal transition) and the mandibular region (chin, mandibular body, angle of the mandible, ascending ramus, and basilar ridge) as the primary anatomical determinants of facial gender. Secondary regions of importance include the nose, zygomatic region, and thyroid cartilage [1,8,15,16]. However, there is a lack of local data in Chile describing the frequency and extent of surgical modifications to these anatomical regions.

Cephalometric differences between male and female facial structures are influenced by biological sex, ethnic background, and genetic inheritance. Typically, male faces have larger craniofacial dimensions, more acute nasolabial angles, and more obtuse mandibular angles, while female face exhibit more convex profiles, smaller nasal dimensions, and less prominent chins [8,15-19].

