### Longitudinal Cohort Study

A prospective longitudinal cohort analytical study following the STROBE (Strengthening the Reporting of Observational Studies in Epidemiology) guidelines [20] will be conducted to evaluate the effects of facial feminization surgery across three primary domains: (1) quality of life, (2) perception and self-perception of facial femininity, and (3) cephalometric and photometric changes in hard and soft facial tissues (Multimedia Appendix 2).

Quality of life will be assessed using the validated questionnaire, administered preoperatively and at least 12 months postoperatively. Femininity perception will be evaluated through standardized facial photographs assessed by independent raters. Cephalometric and photometric changes will be measured using CBCT and analyzed with Dolphin Imaging software (version 12; Dolphin Imaging and Management Solutions).

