###### Femininity Perception Assessment

Femininity will be assessed through both self-perception and third-party evaluation. Self-perceived femininity will be measured using the questionnaire responses regarding this matter.

To assess changes in third-party perception of femininity, a blind evaluation will be conducted using standardized frontal and lateral clinical photographs taken preoperatively and at least 12 months postoperatively. All images will be coded using an alphanumeric identifier (eg, FFS01, for “facial feminization surgery participant 01”), which will not be visible to evaluators. A control group of cisgender women will be included, using anonymized clinical photographs from the Maxillofacial Surgery Service at San Juan de Dios Hospital, authorized for academic and research purposes.

Forty undergraduate students from nonhealth-related fields (eg, arts, philosophy, architecture, and social sciences) at the University of Chile will serve as evaluators. Participants will be recruited through institutional emails and social media platforms.

Inclusion criteria require students to be aged more than 18 years, without training or experience in health, facial anatomy, or aesthetics. Exclusion applies to students with previous engagement with transgender individuals from the hospital’s gender program. Each student will provide informed consent. Evaluators will rate randomized images (including preoperative, postoperative, and control cases) using a 5-point Likert scale ranging from “feminine appearance” (1) to “non-feminine appearance” (5).

Four groups of 10 evaluators each will be formed, ensuring diversity in gender and age. Each group will be randomly assigned a set of photographs, including preoperative, postoperative, and control images, all displayed in a randomized sequence. As a critical methodological safeguard, pre- and postoperative images of the same patient will not be included within the same group to minimize direct comparative bias.

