###### Cephalometric and Photometric Analysis

Facial morphological changes will be measured pre- and postoperatively using CBCT, an imaging software, and extraoral pictures taken in a frontal and lateral view. The following parameters will be assessed: forehead inclination, true vertical distance, nasofrontal angle, mandibular angle, mandibular plane angle, facial profile, nasolabial angle, mentolabial angle, and mentocervical angle.

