##### Data Analysis for the Cohort Study

Descriptive statistics will be used to summarize sociodemographic variables (absolute and relative frequencies). The Shapiro-Wilk test will assess the distribution of continuous variables. Normally distributed variables will be reported as mean and SD; nonnormally distributed variables will be reported as median and IQR. Pre- and postoperative comparisons of continuous variables will be made using paired *t* tests or Wilcoxon signed-rank tests, as appropriate. Categorical variables will be compared using Pearson chi-square or Fisher exact test. Linear regression models will evaluate the associations between cephalometric and photometric changes and perceived femininity scores. Statistical significance will be set at *P*≤.05. All analyses will be conducted using Stata (version 11; StataCorp).

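### The Abstract makes the paired t tests one-tailed, the Methods give no sidedness, and most cohort outcomes have no stated direction; two-sided 5% tests should be stated in both places

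*Protocol article*

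**What the plan says.** The Abstract (Methods) of the Protocol article lists "paired 1-tailed *t* tests or Wilcoxon signed-rank tests, chi-square or Fisher tests, and linear regression models". The operative section, Data Analysis for the Cohort Study, reads: "Pre- and postoperative comparisons of continuous variables will be made using paired *t* tests or Wilcoxon signed-rank tests, as appropriate". The same section adds "Statistical significance will be set at *P*≤.05". It does not mention tails, and no reason for one tail is given anywhere.

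On direction, the document says the following:

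- **Objective (Abstract).** The second aim is to evaluate postoperative change in quality of life, perceived femininity and the facial measurements. No direction is attached.
- **Objectives of the Study.** Improvement is hypothesised for quality of life. No directional hypothesis is set for the other outcomes.
- **Background.** It reports that "male faces have larger craniofacial dimensions, more acute nasolabial angles, and more obtuse mandibular angles", and that female profiles are more convex.
- **Cephalometric and Photometric Analysis.** Nine parameters are listed: "forehead inclination, true vertical distance, nasofrontal angle, mandibular angle, mandibular plane angle, facial profile, nasolabial angle, mentolabial angle, and mentocervical angle".
- **Femininity Perception Assessment.** "Femininity will be assessed through both self-perception and third-party evaluation". Raters use a scale from 1 (feminine) to 5 (non-feminine).

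On status, the section Longitudinal Cohort Study says the cohort will "evaluate the effects of facial feminization surgery across three primary domains". The cohort sample-size section and the Discussion describe the analyses as exploratory.

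**The concern.** The only sidedness the document states is one-tailed, and it appears only in the Abstract. This raises three problems.

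1. **The two sections can be read differently.** A reader of the Methods would probably assume two-sided tests; a reader of the Abstract would not. In the Abstract, the word sits in front of the t test only. Because the choice between t and Wilcoxon follows the data distribution, the same outcome could be tested with one tail or two depending on the result of a normality check.
2. **A tail has to be defined for each outcome.** The document does this, at most, for quality of life. If a tail is picked after the data are seen, a nominal 5% test has a real error of 5% + 5% = 10%.
3. **The error is asymmetric.** This is an uncontrolled before-after study of surgery, intended to inform clinical decisions and policy. A one-tailed test for improvement lowers the bar for claiming benefit and leaves no formal result for deterioration.

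**Working it through.** **The plan's own figure.** The document gives no power, effect size or SD, so there is no power figure to reproduce. Its only cohort calculation is a precision one: 30 from a population of 70, 95% confidence, 12% margin. With a two-sided z of 1.96 and an assumed proportion of 0.5, n0 = 1.96² × 0.25 / 0.12² = 66.7, and n = 66.7 / (1 + 65.7/70) = 34.4, so 35 rather than 30. That is a separate matter. It does not settle sidedness, and nothing below depends on it beyond taking n = 30.

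**Which outcomes have a direction.** The minimum count of before-after comparisons is 9 morphological parameters + 2 femininity measures + 1 quality-of-life comparison = 12.

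- Quality of life: improvement hypothesised (1).
- Nasolabial angle, mandibular angle, facial profile: a male-female difference is described, though not as a hypothesis about change (3).
- Forehead inclination, true vertical distance, nasofrontal angle, mandibular plane angle, mentolabial angle, mentocervical angle: no direction given for the parameter (6).
- Self-perceived and third-party femininity: no hypothesis stated (2).

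So 6 + 2 = 8 of 12 have no stated direction, or 6 of 12 if greater femininity is taken as implied for the last two.

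**Threshold.** With 30 complete pairs (29 degrees of freedom), the critical t is 1.699 for a one-sided 5% test and 2.045 for a two-sided 5% test. One-sided 5% uses the same cut-off as two-sided 10%.

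**A true worsening of 0.5 SD** (SD of the paired differences; an illustrative size, since the document gives none). The noncentrality is 0.5 × √30 = 2.74 in the unfavourable direction.

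- One-sided test for improvement: probability of rejection below 0.00001.
- Two-sided 5% test: probability of a significant worsening 0.754, about 75%.

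**Price of two-sided testing** (noncentral t, n = 30):

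| | One-sided 5% | Two-sided 5% |
|---|---|---|
| Detectable change at 80% power | 0.465 SD | 0.529 SD |
| Power for a 0.5 SD improvement | 0.848 | 0.754 |

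The detectable change rises by a factor of 0.529 / 0.465 = 1.14.

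**Number of tests.** If all 12 nulls were true and the tests independent, the chance of at least one false positive at 5% each is 1 − 0.95¹² = 0.460. In simulation with 12 equally correlated one-sided tests it is 34%, 27% and 16% at correlations of 0.3, 0.5 and 0.8. The 0.460 is the same for one-sided and two-sided 5% tests, so it does not measure the one-tailed problem.

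**The case against.** The strongest reply is that the Methods section governs, that silence there is conventionally read as two-sided, and that the Abstract contains a loose phrase. Further, a directional hypothesis is stated for quality of life, and a one-tailed 5% test of it is valid and has exactly the error it claims; it is only lenient against the two-sided convention. Differing directions across angles, or a rater scale on which lower is better, do not prevent one-tailed testing, because a lower tail can be specified.

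Much of this stands. The reversed rater scale is no argument against one tail, and for quality of life alone a one-tailed test could be defended. But the reply needs a tail for every outcome, and most have none. Nor can silence in the Methods be relied on to override the only explicit statement in the document.

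A reader might go further and infer that harm could not be detected. That is too strong. It requires the Abstract to govern, the tail to be improvement and the t test to be the one used. Even then, means with SDs or medians with IQRs are to be reported and would show a worsening; what is lost is the significance label.

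A reader might also infer that chance positives are likely and that adjustment is obligatory. The 46% is below one half and assumes 12 independent true nulls, which is hard to sustain for an operation that deliberately reshapes the structures measured. The analyses are called exploratory, and an outcome hierarchy or adjustment rule may sit in an analysis plan that is not shown.

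**Conclusion.** The point holds as a correction to stated text: the Abstract and the Methods do not agree on sidedness, and the one sidedness given does not fit a non-directional objective or outcomes that mostly lack a direction. Where the one-tailed test applies, the bar for claiming benefit is that of two-sided P≤.10, and a 0.5 SD worsening that a two-sided test would flag about three times in four would almost never be declared significant.

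These figures assume 30 complete pairs, roughly normal paired differences, and a tail set towards improvement. The document itself expects some attrition; with fewer pairs, power falls and the detectable change rises.

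The number of comparisons is a secondary matter of labelling. Calling three domains primary sits awkwardly beside analyses called exploratory, but the document does not support treating the lack of an adjustment as an error.

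**What to change.** State in both the Abstract and Data Analysis for the Cohort Study that the paired t test and the Wilcoxon signed-rank test are two-sided at 5%. Report every before-after change with a two-sided 95% confidence interval, so that the size and direction of any change can be read whatever the P value.

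Optionally, add a sentence describing the 12 or more unadjusted comparisons as exploratory, to reconcile the three primary domains with the exploratory label. A Holm adjustment over the nine morphological parameters is not required. It would be a real trade-off: its first step is at 0.05 / 9 = 0.0056, where the detectable change at n = 30 and 80% power is about 0.71 SD. Naming a quality-of-life total score as the sole primary outcome cannot simply be written in either, because no such score is defined in the document.

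The required change is one of wording. Its statistical cost is the rise in detectable change from 0.46 to 0.53 SD. On the stated schedule, with surgeries through 2026 and the postoperative questionnaire starting 12 months after surgery, it can be made before postoperative outcome data exist.

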**Results:**

This study was funded in October 2023. Phase 1 (January 2024 to January 2025) included 216 participants, exceeding the minimum sample size requirement. Data analysis is ongoing, and results will be reported separately. Phase 2 is in progress, with preoperative cone beam computed tomography scans and photographs being collected. The validated preoperative questionnaire will be administered in late 2025, with surgeries scheduled throughout 2026. Data collection is expected to conclude in 2027.

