##### Sample Size Calculation for Cohort Study

The gender program at San Juan de Dios Hospital currently includes 70 transgender women undergoing hormone therapy and attending regular medical follow-up appointments. On the basis of this population size, a sample of 30 participants was calculated using a 95% confidence level and an estimated margin of error of 12%. This adjustment reflects logistical and ethical considerations related to long-term follow-up while maintaining sufficient statistical validity for exploratory analyses of surgical outcomes.

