##### Data Collection

###### Quality of Life Assessment

Participants in the cohort study will complete the validated quality-of-life questionnaire before surgery and again at 12 months postoperatively.

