## Results

This study was funded in October 2023. Phase 1, corresponding to the development and initial psychometric validation of the Quality of Life and Perception of Femininity in Facial Feminization Surgery questionnaire, was conducted between January 2024 and January 2025. A total of 216 transgender women participated in the study, which exceeded the estimated sample size.

The initial questionnaire design was based on a structured literature review conducted according to PRISMA guidelines, which identified existing tools and dimensions used to assess the quality of life of transgender women undergoing facial feminization surgery (Multimedia Appendices 3 and 4). Data analysis is currently in progress, and the corresponding manuscript is expected to be submitted for publication before the end of 2025.

Concurrently, phase 2 of the study—the longitudinal cohort assessing surgical outcomes—is ongoing. Standardized facial photographs and CBCT scans are being collected for presurgical cephalometric and photometric analysis.

The validated presurgical quality-of-life questionnaire will be administered starting in the fourth quarter of 2025 to more than 30 transgender women currently on the waiting list for facial feminization surgery. The surgeries are planned to take place throughout 2026, with the administration of the postsurgical quality-of-life questionnaire starting 12 months after surgery. Data collection is expected to conclude in 2027.

All relevant data underlying the preliminary findings of this study will be made available through the openICPSR repository. Data will be deidentified to protect participant confidentiality in accordance with ethical guidelines. Access to sensitive data that cannot be fully anonymized will be restricted because of ethical considerations. Requests for access to restricted data can be directed to the Scientific Ethics Committee of San Juan de Dios Hospital, Santiago, Chile, and will be considered on a case-by-case basis.

In case of early study termination, an ethically responsible discontinuation plan will be implemented, including notification to the ethics committee and participants, documentation of reasons, appropriate data analysis, and submission of a final report to ensure transparency and scientific value.

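### The stated calendar puts an unequal wait of about 0 to 15 months between the baseline questionnaire and surgery, and the paired analysis counts any change during it as the effect of surgery

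*Protocol article*

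**What the plan says.** **Baseline timing.** The Results paragraph of the abstract says: "The validated preoperative questionnaire will be administered in late 2025, with surgeries scheduled throughout 2026". The main Results section says that the form "will be administered starting in the fourth quarter of 2025 to more than 30 transgender women currently on the waiting list for facial feminization surgery". In the Methods, baseline is anchored only to the operation, with no maximum interval: under Quality of Life Assessment, participants "will complete the validated quality-of-life questionnaire before surgery and again at 12 months postoperatively".

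**Surgery and follow-up timing.** The main Results section continues: "The surgeries are planned to take place throughout 2026, with the administration of the postsurgical quality-of-life questionnaire starting 12 months after surgery". The second form is described in three ways:

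- Abstract (Methods) and Quality of Life Assessment: 12 months after surgery.
- Longitudinal Cohort Study: "administered preoperatively and at least 12 months postoperatively". The postoperative photographs under Femininity Perception Assessment have the same open-ended minimum.
- Main Results: from 12 months after surgery onward, as quoted above.

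The abstract and the main Results section both expect data collection to end in 2027.

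**Analysis.** Data Analysis for the Cohort Study says: "Pre- and postoperative comparisons of continuous variables will be made using paired" (the named options are a t test and the Wilcoxon signed-rank test). It names no adjustment for time between measurements. The only control group is a set of photographs of cisgender women, used for the third-party ratings. Self-perceived femininity comes from the questionnaire, so it shares the questionnaire's timing. The Longitudinal Cohort Study section presents the comparison as an evaluation of the effects of surgery.

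**The concern.** Follow-up is counted from each woman's operation, but the stated calendar sets baseline by date. A woman operated on in January 2026 has a baseline close to surgery. A woman operated on in December 2026 has one about a year old or more. Quality of life and self-rated femininity can move in that time for reasons other than the operation. The Objectives section itself lists employment, social participation and psychosocial stress as variables to examine, and all three can change within a year.

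A paired comparison without a comparator cannot separate change during the wait from change after surgery. The unequal waits also mean that the paired differences cover different lengths of time, so the average change depends partly on how the surgical list was filled. Two of the three primary domains are affected: quality of life, and self-perceived femininity. The limitations in the Discussion do not mention the wait.

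**Working it through.** **Inputs from the protocol article**

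- Baseline form: fourth quarter of 2025, so 1 October to 31 December 2025 if the abstract's late-2025 timing is followed.
- Surgery: 1 January to 31 December 2026.
- Second form: 12 months after surgery at the earliest; collection ends by 31 December 2027.
- Cohort size 30; significance level 0.05; the abstract says 1-tailed, and the analysis section does not state sidedness.

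The protocol gives no figure for the wait, so there is none to reproduce.

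**Step 1: wait and span.** Wait = surgery date − baseline date. Span = wait + 12 months.

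| Baseline form | Surgery | Wait (months) | Span (months) |
|---|---|---|---|
| 1 Oct 2025 | 1 Jan 2026 | 3.0 | 15.0 |
| 1 Oct 2025 | 1 Jul 2026 | 9.0 | 21.0 |
| 1 Oct 2025 | 31 Dec 2026 | 15.0 | 27.0 |
| 15 Nov 2025 | 1 Jan 2026 | 1.5 | 13.5 |
| 15 Nov 2025 | 1 Jul 2026 | 7.5 | 19.5 |
| 15 Nov 2025 | 31 Dec 2026 | 13.5 | 25.5 |
| 31 Dec 2025 | 1 Jan 2026 | 0.0 | 12.0 |
| 31 Dec 2025 | 1 Jul 2026 | 6.0 | 18.0 |
| 31 Dec 2025 | 31 Dec 2026 | 12.0 | 24.0 |

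The wait runs from 0 to 15 months. The midpoint case is 7.5 months, which is 7.5 / 19.5 = 38% of its span.

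**Step 2: ceiling on the span.** The open-ended follow-up wording does not push the span past 27 months. The last possible second form is on 31 December 2027, and 1 October 2025 to 31 December 2027 is 27 months.

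**Step 3: illustration only.** The protocol gives no rate of change without surgery, so the rate here is assumed. Suppose that surgery has no effect, that nothing changes in the 12 months after it, and that scores improve during the wait by 0.1 to 0.4 SD of the individual change per year. With a 7.5-month wait for everyone:

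- Shift m = rate × 7.5 / 12: 0.1 × 0.625 = 0.0625 SD, up to 0.4 × 0.625 = 0.25 SD.
- Noncentrality = m × √30: 0.0625 × 5.48 = 0.34, up to 0.25 × 5.48 = 1.37, on 29 degrees of freedom.
- Chance that the paired t test is significant: 6% to 26% two-sided, or 10% to 38% 1-tailed, against a nominal 5%.

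If scores worsen during the wait, the sign reverses and a real benefit would be understated. The figures show only that a modest drift would matter at n = 30; they do not estimate the drift.

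**Step 4: after the fix.** If the baseline form falls in, say, the last 4 weeks before surgery, the wait is at most 28 / 30.44 = 0.9 months. The span to a 12-month form is then 12 to 12.9 months for every woman.

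**The case against.** The strongest reply is that the Methods do anchor baseline to surgery and that the calendar is only a progress statement. The fuller text says that administration starts in the fourth quarter of 2025, so some forms could be completed later and nearer to the operation. Exact visit windows are also a detail that an article may leave to the full protocol. This stands in part: the calendar makes a long wait likely for many women but does not fix it for all. It does not remove the point. The abstract places the form in late 2025, the main text sends it to women already on the waiting list, and no section links it to an operation date. The stated schedule itself creates the gap.

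The second reply is that re-timing does not make the comparison causal. That is correct. The 12 months after surgery remain uncontrolled, and the authors call the cohort exploratory. The objective in the abstract speaks of postoperative changes; only some sections go further. What re-timing removes is the additional, unequal and avoidable part.

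A reader might infer more than the documents support:

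- **That most women wait 15 months.** This is the extreme case: a form on 1 October 2025 and surgery on 31 December 2026.
- **That continuing hormone therapy drives the change.** The sample-size section says that the program has "70 transgender women undergoing hormone therapy", but nothing gives the duration or stability of therapy among women listed for surgery.
- **That the result is biased toward benefit.** No passage gives a rate or direction of change during the wait.

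**Conclusion.** The point holds as a defect of timing. On the stated calendar the wait is about 0 to at most 15 months (7.5 months at the midpoint), and the pre-post span is about 12 to at most 27 months. Both vary with place in the queue. Any change in quality of life or self-rated femininity during the wait is included in the reported change. How much, and in which direction, is unknown.

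The range assumes that baseline forms are completed within the fourth quarter of 2025. Forms completed later would shorten the wait. The midpoint figure also assumes surgeries centered on mid-2026.

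The conflict in follow-up wording is real but secondary. This is a cheap improvement that should be made, not a fault that invalidates the cohort. It is urgent only because a near-surgery baseline cannot be collected once the woman has been operated on.

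**What to change.** 1. **Baseline.** Administer, or repeat, the online questionnaire within one short fixed window before each operation (for example the last 4 weeks), and name that form as the baseline for quality of life and self-rated femininity.
2. **Run-in.** Keep any earlier late-2025 form. Report the change from it to the preoperative form, with each woman's interval, as a description of change without surgery.
3. **Follow-up.** Replace the three descriptions with one window, used in every section. It must fit the end of collection: surgery on 31 December 2026 reaches 12 months on 31 December 2027, so a window of, say, ±1 month would run into January 2028. Either choose a window that fits or move the end of collection.
4. **Wording.** In the Longitudinal Cohort Study section, describe the result as change after surgery rather than its effects, and add the uncontrolled postoperative year to the limitations.

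The cost is at most one extra self-administered online form per woman, and none for a woman whose first form already falls inside the window. No extra imaging or visits are needed, and the mobile messaging already planned for retention can carry the link.
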